### Sample size

Time to lasting RTW is the primary outcome measure for the power calculation. In order to calculate the sample size we assumed that a Hazard Ratio (HR) of 2.0 is the smallest clinical and societal relevant ratio. A HR of 2.0 indicates that employees in the intervention group return to work twice as quickly as employees in the control group. This HR is based on recent studies in occupational health care on RTW of short-term sick-listed employees with low back pain and adjustment disorders[11,25,27,28]. Assuming that a minimum of 2/3 of the participants achieve a full RTW during the follow-up, the calculation showed that a sample size of 98 employees is needed (a power of (1-β =) 0.80 and a two-sided significance level of 0.05 (α)). Since the OPs, because of their role and function in the RTW process, may influence the RTW date, a multilevel analysis on the level of the OP is taken into account. For 13 OPs and an intraclass correlation coefficient (ICC) of 0.05 (clustering in our groups is not presumed to be large) a total of 130 employees are needed. When taking into account a loss to follow-up of 10%, 144 employees have to be enrolled in the study. Although loss to follow-up is taken into account, we do not expect a high loss to follow-up in this study because data about the primary outcome (lasting RTW) will be acquired from the continuous company registration systems after the one-year follow-up.

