### Randomisation procedure

An independent statistician prepared the randomisation by using a computer-generated randomisation. To prevent unequal randomisation, employees are pre-stratified by company and whether they are on full or part-time sick leave. Furthermore, block randomisation (with blocks of four) is applied to ensure equal group sizes within each stratum. The researchers prepared sealed envelopes before the start of the study containing either a referral to the workplace intervention group or the usual care group. If the baseline questionnaire is completed, each employee can choose one of the two succeeding envelopes of the correct stratum provided by the researcher. The employee is asked to open the envelope and write down his or her name and the date on the note that contains the randomisation result.

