#### Prognostic measures

Sick leave in the past year, burnout and expectations of the employee about the duration of absence[35] are considered to be potentially prognostic for RTW. Burnout is measured by the Utrecht Burnout Scale-General Survey UBOS[36], the Dutch version of the Maslach Burnout Inventory [37]. In addition, the amount of psychosocial problems may be a prognostic factor for CMDs and sick leave. Psychosocial problems over the last 6 months are measured by the BIOPRO questionnaire [38].

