### Statistical analyses

All statistical analyses will be performed at employee level, according to the intention-to-treat principle. In order to assess whether protocol deviations have caused bias, the results of the intention-to-treat analyses will be compared to per protocol analyses, excluding those employees who were not treated according to the intervention protocol. Baseline characteristics of employees in the two groups will be compared using descriptive statistics. If necessary, analyses will be adjusted for prognostic dissimilarities.

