#### Effect evaluation

Survival analysis will be used to analyse sick leave data with regard to the first period of sick leave. To describe the sick leave duration until lasting RTW in both groups, the Kaplan Meier method will be used. The Cox proportional hazard model will be applied to calculate hazard ratios. If appropriate standard errors will be corrected for clustering. Differences in total days of sick leave during the year of follow-up will be analysed by using the Student's T-test. Longitudinal random coefficient analyses will be used to assess differences in secondary outcome measures. Intraclass correlation coefficients will be calculated.

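### Adjustment that depends on observed baseline imbalance will normally leave out the stratification factors and leaves the primary model open; the analysis stays valid but gives up power

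*Protocol article*

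**What the plan says.** All references are to the protocol article.

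- **Randomisation procedure:** "employees are pre-stratified by company and whether they are on full or part-time sick leave", with blocks of four within each stratum.
- **Prognostic measures:** past-year sick leave, burnout and "expectations of the employee about the duration of absence[35] are considered to be potentially prognostic for RTW". The amount of psychosocial problems is named as a further possible prognostic factor.
- **Statistical analyses:** the arms are first compared descriptively at baseline. Then: "If necessary, analyses will be adjusted for prognostic dissimilarities".
- **Statistical analyses, Effect evaluation:** a Cox model gives the hazard ratio, with no stratum or covariate named. A correction of standard errors for clustering is conditional. For the secondary outcome, "Differences in total days of sick leave during the year of follow-up will be analysed by using the Student's T-test".
- **Co-interventions and compliance:** a second conditional option allows adjustment for baseline co-interventions.

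**The concern.** A factor used to stratify the randomisation should normally also be in the analysis, and covariates should be chosen for their expected prognostic strength before the data are seen. The stated rule works the other way. It looks for differences between the arms, and stratified blocking is there to prevent differences in company and sick-leave status. The two factors thought important enough to stratify on are therefore the least likely to be adjusted for. The other measures come in or stay out according to chance imbalance.

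This goes beyond detail left to an analysis plan. The article states a rule, and a later plan would have to replace it.

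Two things are at stake. In a Cox model, leaving out a prognostic factor moves the estimated hazard ratio towards 1 relative to the conditional effect and lowers power, even with balanced arms. And with no criterion, covariate list or statement of which result is primary, more than one analysis could be presented as the planned one.

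**Working it through.** **Inputs from the article (Sample size).** The effect: "a Hazard Ratio (HR) of 2.0 is the smallest clinical and societal relevant ratio". The events: "a minimum of 2/3 of the participants achieve a full RTW during the follow-up". The design: "a sample size of 98 employees is needed (a power of (1-β =) 0.80", with "a two-sided significance level of 0.05". There are 13 occupational physicians (OPs), an intraclass correlation of 0.05 and 10% loss to follow-up.

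**Reproducing the plan's figures.**
- Events (Schoenfeld, 1:1): 4 × (1.960 + 0.842)² / (ln 2)² = 65.35. Employees: 65.35 / (2/3) = 98.02, stated as 98.
- Clustering: design effect 1 + (98/13 − 1) × 0.05 = 1.327, and 98 × 1.327 = 130.04, stated as 130.
- Loss to follow-up: 130 / 0.9 = 144.4, stated as 144.

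The three figures reproduce, and the point below does not change them.

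**Simulation.** There were 2,500 trials per scenario with 98 employees. That is the size before inflation for clustering, so it is the right reference for 80% power when no clustering is simulated. Allocation was in blocks of four within strata, times were exponential and censored at one year, 2/3 had events overall, and the conditional hazard ratio was 2.0.

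**Assumptions not in the article.** There are two stratification factors, each with two equal-sized levels and a hazard ratio between 1.0 and 2.0, and one continuous baseline predictor with a log hazard ratio between 0 and 0.7 per SD. Because no trigger is stated, the conditional rule is represented by adjusting for the predictor only when its baseline difference has |z| > 1.645.

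| HR per factor | Predictor, log-HR per SD | Unadjusted HR | Power, unadjusted | Power, conditional rule | Power, factors in model | Power, factors and predictor |
|---|---|---|---|---|---|---|
| 1.0 | 0 | 2.03 | 81.4% | 81.2% | 81.7% | 81.4% |
| 1.25 | 0 | 2.00 | 78.8% | 78.8% | 80.0% | 79.5% |
| 1.5 | 0 | 1.94 | 76.6% | 76.0% | 80.3% | 79.4% |
| 2.0 | 0 | 1.88 | 71.8% | 71.5% | 79.6% | 78.6% |
| 1.5 | 0.5 | 1.85 | 68.9% | 69.6% | 72.5% | 79.2% |
| 2.0 | 0.7 | 1.71 | 57.5% | 59.0% | 64.8% | 79.4% |

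- **Stratification factors alone:** the loss is 80.0 − 78.8 = 1.2, 80.3 − 76.6 = 3.7 and 79.6 − 71.8 = 7.8 points.
- **Factors at 1.5 plus one moderate predictor (0.5 per SD):** 79.2 − 68.9 = 10.3 points. The conditional rule recovers 69.6 − 68.9 = 0.7 of them, because chance imbalance seldom triggers it.
- **Nothing prognostic:** 81.4% against 81.4%, so prespecified adjustment costs nothing.
- **No treatment effect:** with prognostic factors present, the unadjusted test rejects in 3.8% to 3.9% of trials and the fully adjusted test in 5.0% to 5.1%. The mean estimate is 1.00 under both. Taking the better of the unadjusted and predictor-adjusted results gives 5.6% to 5.8%.

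**The case against.** **The article is condensed and the analysis plan is not shown.** Naming strata and covariates can be left to that plan, and the article mentions multivariate analyses. This stands against a charge based on silence alone. It does not rescue the stated rule, which makes adjustment depend on dissimilarity.

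**A reader might infer that the hazard ratio is biased and the trial underpowered.** The documents do not support that. The shift towards 1 is non-collapsibility: the unadjusted model estimates a marginal effect and the adjusted model a conditional one. The Sample size section explains a hazard ratio of 2.0 as a contrast between groups, which fits a marginal reading. If the marginal hazard ratio is about 2.0, a simulation with 98 employees and no strata keeps unadjusted power at 80% (predictor 0.5 per SD, conditional hazard ratio 2.17) and 79% (0.7 per SD, 2.33). Adjustment then raises power to 86% and 91%. On that reading there is no shortfall against the plan, only unused power.

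**A reader might infer that covariates will be picked from unblinded tables and inflate false positives.** The Blinding section says data are entered under a research code and analysed blind, and registry outcomes are obtained only after follow-up. That protection is imperfect, since the same section says the researcher knows the allocation. Even so, choosing the better of two results gave only 5.6% to 5.8%, and omitting the factors lowers the error rate.

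**Prognostic strength is unknown.** The article calls the measures only potentially prognostic. This stands, so the size of the loss is a range and not an estimate. The t-test concerns a secondary outcome, and there too the consequence of ignoring the strata is conservatism.

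**Conclusion.** The point holds as one of efficiency and prespecification, not of validity. The stated rule would normally keep company and sick-leave status out of the primary model, would use the prognostic measures only by chance, and does not fix which model is primary.

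For a conditional hazard ratio of 2.0, 98 employees and no clustering, the cost is about 1 to 8 points of power for stratification-factor hazard ratios of 1.25 to 2.0. It is about 10 points with factors at 1.5 and one further moderate predictor, and nil if nothing is prognostic. Losses above 20 points appear only under the strongest assumptions tried (79.4 − 57.5 = 21.9 points), for which the article offers no support. The direction is firm whenever the factors are prognostic; the size rests on assumed strengths. The change should be made because it costs nothing when the factors turn out to be uninformative.

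**What to change.** Replace the conditional sentence in Statistical analyses with wording such as: *The primary Cox model will be stratified by (or adjusted for) company and full or part-time sick leave, and adjusted for a short list of the baseline measures named under Prognostic measures, fixed before outcome data are seen, regardless of observed imbalance. Clustering by OP is handled as planned. The unadjusted hazard ratio is reported as a sensitivity analysis.*

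The sponsor should choose the measures. The list should be short, because the design yields about 65 events at 98 employees and at most 144 × 2/3 = 96 at full enrolment. The conditional option for baseline co-interventions should be settled at the same time. Total sick-leave days should be analysed with a linear model using the same strata and covariates in place of the t-test.

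The cost is wording only: the stratification factors are known at randomisation, the prognostic measures are already planned, and the sample size does not change. The adjusted hazard ratio is a conditional effect and should be labelled so.

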#### Effect evaluation

Survival analysis will be used to analyse sick leave data with regard to the first period of sick leave. To describe the sick leave duration until lasting RTW in both groups, the Kaplan Meier method will be used. The Cox proportional hazard model will be applied to calculate hazard ratios. If appropriate standard errors will be corrected for clustering. Differences in total days of sick leave during the year of follow-up will be analysed by using the Student's T-test. Longitudinal random coefficient analyses will be used to assess differences in secondary outcome measures. Intraclass correlation coefficients will be calculated.

#### Cost-effectiveness evaluation

Direct, indirect and total costs will be computed for each employee. Bootstrapping will be used for pair-wise comparison of the mean groups to calculate mean differences in direct, indirect and total costs between the two groups of employees. Confidence intervals (95%) will be obtained by bias corrected and accelerated bootstrapping. To assess the cost-effectiveness ratios of the workplace intervention, the difference in mean costs between the groups will be divided by the difference in RTW between the groups. These ratios will be graphically presented in a cost-effectiveness plane. Acceptability curves will also be presented. Similarly, utility assessed with the EuroQol EQ-5D will be used to estimate the incremental costs per QALY gained in a cost-utility analysis.

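### The cost bootstrap is written as a plain two-group comparison that does not use the randomisation strata, so the cost intervals may be wider than the design allows (minor; size depends on how well the strata predict cost)

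*Protocol article*

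**What the plan says.** Under Randomisation procedure, "employees are pre-stratified by company and whether they are on full or part-time sick leave", and "block randomisation (with blocks of four) is applied to ensure equal group sizes within each stratum".

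Under Statistical analyses, Cost-effectiveness evaluation, the method for costs is: "Bootstrapping will be used for pair-wise comparison of the mean groups to calculate mean differences in direct, indirect and total costs between the two groups". The next sentence reads "Confidence intervals (95%) will be obtained by bias corrected and accelerated bootstrapping". The same differences feed the cost-effectiveness ratios, the plane and the acceptability curves. Neither stratification factor is mentioned there.

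The opening paragraph of Statistical analyses adds a general clause: "If necessary, analyses will be adjusted for prognostic dissimilarities". It follows a descriptive comparison of baseline characteristics and does not name the strata.

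Under Outcomes, Cost-effectiveness evaluation, productivity cost is built from days of full or partial sick leave and from earnings, while direct cost comes from a health-care use questionnaire. The protocol gives no cost standard deviation, no cost by stratum and no expected interval width.

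**The concern.** Stratified blocks force the two arms to have nearly the same mix of companies and of full and part-time leave. Differences in cost between strata therefore cannot contribute much to the difference between arms. A two-group bootstrap that resamples each arm as one pool does not know this: the stratum mix varies from resample to resample, and that variation enters the interval.

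The general adjustment clause is unlikely to repair this. It responds to dissimilarity between arms, and blocking makes the arms similar on exactly these two factors.

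Whether it matters depends on whether the strata predict cost. Full versus part-time leave at entry is an early reading of the lost time that drives productivity cost. Earnings may differ between a university with its medical center and a steel company. Both links are inferences. At stake is the precision of the cost comparison in a trial whose stated objective is cost-effectiveness and whose sample was sized for time to return-to-work, not for costs.

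**Working it through.** **The plan's own figure.** There is none for costs, so the sample size was reproduced to fix N for the checks. Inputs from the Sample size section: "we assumed that a Hazard Ratio (HR) of 2.0 is the smallest clinical and societal relevant ratio", "a power of (1-β =) 0.80 and a two-sided significance level of 0.05 (α", two thirds returning to work, 13 occupational physicians, ICC 0.05 and 10% loss.
- Events (Schoenfeld, 1:1): 4 × (1.960 + 0.842)² / (ln 2)² = 65.35.
- Employees: 65.35 / (2/3) = 98.0. Stated: 98.
- Design effect: 1 + (98/13 − 1) × 0.05 = 1.327; 98 × 1.327 = 130.0. Stated: 130.
- Loss: 130 / 0.9 = 144.4. Stated: 144.

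The figures reproduce. They do not bear on the point, except that N = 144 is used below.

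**Width.** Let R² be the share of cost variance explained by the strata (assumed; not in the protocol). With 1:1 allocation within strata, the variance of the difference in means contains only the within-stratum part, (1 − R²) of the total. The plain interval uses the total, so plain width / adjusted width = 1/sqrt(1 − R²). Under normal theory the plain 95% interval covers 2Φ(1.96/sqrt(1 − R²)) − 1.

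| Assumed R² | Width ratio | Excess width | Normal-theory coverage |
|---|---|---|---|
| 0 | 1.000 | 0% | 95.0% |
| 0.02 | 1.010 | 1.0% | 95.2% |
| 0.05 | 1.026 | 2.6% | 95.6% |
| 0.10 | 1.054 | 5.4% | 96.1% |
| 0.20 | 1.118 | 11.8% | 97.2% |
| 0.30 | 1.195 | 19.5% | 98.1% |

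Simulated standard errors (144 employees, four equal strata, 1:1 within stratum, lognormal costs) agree. At R² of 0, 0.10, 0.20 and 0.30 the plain standard error was 1.00, 1.05, 1.12 and 1.20 times the true sampling SD under mild skew (log-SD 0.4), and 1.00, 1.05, 1.12 and 1.19 times under strong skew (log-SD 1.0). Four equal strata is an assumption; the protocol states neither their number nor their sizes.

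**Coverage of the planned interval type.** Bias-corrected and accelerated (BCa) intervals were simulated with the same layout in blocks of four (1,200 runs, 800 resamples). The comparator resampled within strata.

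| R² | Mild skew: plain / stratified | Strong skew: plain / stratified |
|---|---|---|
| 0 | 94.2% / 93.2% | 89.3% / 89.3% |
| 0.05 | 94.9% / 94.0% | 90.7% / 88.0% |
| 0.10 | 94.8% / 93.2% | 92.6% / 89.3% |
| 0.20 | 96.6% / 93.2% | 94.8% / 90.2% |

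The Monte Carlo standard error is about 0.6 to 0.9 percentage points.

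Two readings follow. First, plain coverage tends to rise with R², as the width formula predicts. Second, under strong skew it starts at 89.3% where the strata play no part, so under-coverage of BCa is a separate effect that can offset the excess width. Covariate-adjusted BCa intervals, simulated separately, also covered only 89% to 91% in the strongly skewed case.

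In these runs the simulated BCa width ratio at R² = 0 was 1.02, not 1.00. That is a small-cell artefact of resampling within strata: with 18 per arm and stratum against 72 per arm, sqrt((71/72)/(17/18)) = 1.022. It is one reason to prefer covariate adjustment to resampling within small strata.

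**The case against.** The strongest reply is that silence is being read as a choice. The article says that group means are compared by bootstrap; it does not say that resampling is unstratified or that covariates are excluded. A condensed design article often leaves such detail to the full analysis plan, and the general clause leaves adjustment open. This stands in part: a reader should not infer that the trial team decided to ignore the strata. What remains is that the method as stated is a comparison of raw group means, and the only adjustment provided for would rarely select factors that blocking has already balanced.

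The second reply is that excess width is conditional. The protocol gives no R², at R² = 0 nothing is lost, and up to 0.10 the excess is under 6%. This stands in full. So does the narrower point on direct costs: nothing in the protocol ties either stratum to health-care use.

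The third reply concerns coverage. A reader might infer that the planned intervals are simply too wide. The simulations do not support that. With strongly skewed costs, plain BCa coverage stayed below 95% at every R² tried. Wider than an adjusted interval is not the same as wider than nominal.

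**Conclusion.** The plan as written does not use stratum information that the trial already holds. To the extent that company and full or part-time leave predict cost, the reported intervals for lost-productivity and total cost will be wider than the design allows: 0% at R² = 0, about 3% at 0.05, 5% at 0.10 and 12% at 0.20. All R² values are assumed.

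This is a possible loss of precision. It is not bias, since near-equal allocation within strata leaves the point estimate almost unchanged, and it creates no false-positive risk. The protocol does not support the stronger statements that the intervals are demonstrably too wide, that all three cost comparisons are affected, or that the analysis is in error. Severity is minor; this is an inexpensive improvement to a stated method.

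**What to change.** State that each cost difference and each effect difference (return-to-work, QALYs) is estimated from a model with arm, company and full or part-time leave at randomisation, refitted in every bootstrap resample. Use the same adjusted estimates for the cost-effectiveness ratios, the plane and the acceptability curves. If a full analysis plan already says this, a cross-reference is enough.

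Keep the BCa interval, but check its coverage by simulation on costs as skewed as those observed, against an alternative such as a normal-theory interval with the stratum-based standard error. In the strongly skewed simulations that alternative covered 95% to 96%. This check matters because adjustment narrows the interval and could expose under-coverage that the excess width now masks.

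The cost is a sentence or two of analysis wording and a few lines of code. Both factors are recorded at randomisation, so no new data and no change to sample size are needed.

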**Methods:**

The study is designed as a randomized controlled trial with a follow-up of one year. Employees eligible for this study are on sick leave for 2 to 8 weeks with common mental disorders. The workplace intervention will be compared with usual care. The workplace intervention is a stepwise approach that aims to reach consensus about a return-to-work plan by active participation and strong commitment of both the sick-listed employee and the supervisor. Outcomes will be assessed at baseline, 3, 6, 9 and 12 months. The primary outcome of this study is lasting return-to-work, which will be acquired from continuous registration systems of the companies after the follow-up. Secondary outcomes are total number of days of sick leave during the follow-up, severity of common mental disorders, coping style, job content, and attitude, social influence, and self-efficacy determinants. Cost-effectiveness will be evaluated from the societal perspective. A process evaluation will also be conducted.

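### Baseline EQ-5D is not a prespecified covariate for the QALY difference; any adjustment rests on an undefined, data-dependent rule

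*Protocol article*

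**What the plan says.** Under Statistical analyses, the Cost-effectiveness evaluation subsection describes the economic analysis in terms of group differences. For costs: "Bootstrapping will be used for pair-wise comparison of the mean groups to calculate mean differences in direct, indirect and total costs". For the cost-effectiveness ratio, "the difference in mean costs between the groups will be divided by the difference in RTW between the groups". After mentioning the cost-effectiveness plane and acceptability curves, it turns to QALYs and says that, in the same manner, "utility assessed with the EuroQol EQ-5D will be used to estimate the incremental costs per QALY gained in a cost-utility analysis". It does not say how QALYs are built from the EQ-5D, and it names no regression model or covariate.

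The opening paragraph of Statistical analyses, which stands above both the effect and the economic subsections, says: "Baseline characteristics of employees in the two groups will be compared using descriptive statistics". It then adds: "If necessary, analyses will be adjusted for prognostic dissimilarities". No variables and no criterion are given.

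Three other places bear on the point:

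- Prognostic measures lists past-year sick leave, burnout, the employee's expected duration of absence, and psychosocial problems. EQ-5D is not on the list.
- Randomisation procedure stratifies by company and by full or part-time sick leave, not by health utility.
- The Abstract gives the general schedule: "Outcomes will be assessed at baseline, 3, 6, 9 and 12 months". No separate schedule is given for the EQ-5D.

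**The concern.** The RTW outcome is counted from randomisation, so it has no baseline value inside it. A QALY does. In the usual area-under-the-curve construction, baseline utility is the first point of the curve, and it also predicts the later points. A template that suits RTW therefore leaves something out when it is carried over to QALYs.

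With 65 to 72 employees per arm and no stratification on utility, some chance difference in baseline EQ-5D is to be expected. If the QALY difference is not adjusted, part of that difference appears as treatment effect in the denominator of the cost-per-QALY ratio. The standard error is also larger than it need be.

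The general adjustment clause leaves it open, until the baseline data have been seen, whether this is dealt with. Cost-effectiveness is the stated objective of the trial, so a choice made at that stage is undesirable.

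**Working it through.** **Numbers per arm.** No stated figure is in dispute; the sample size only sets how large a chance imbalance is likely to be. It reproduces from the inputs in the Sample size section:

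- Events: (1.96 + 0.8416)² × 4 / (ln 2)² = 65.35. Divided by 2/3, this gives 98.02 (stated: 98).
- Design effect with 13 OPs and ICC 0.05: 1 + (98/13 − 1) × 0.05 = 1.327. Then 98 × 1.327 = 130.04 (stated: 130).
- Loss of 10%: 130 / 0.90 = 144.4 (stated: 144).

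This gives 130/2 = 65 to 144/2 = 72 per arm.

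**Assumptions, not in the documents.** EQ-5D utility SD 0.25 at every wave (range 0.15 to 0.30 for the imbalance); equal correlation r between waves of 0.3, 0.5 or 0.7; EQ-5D measured at 0, 3, 6, 9 and 12 months; QALY by the trapezoid rule, with weights 0.125, 0.25, 0.25, 0.25, 0.125.

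**Likely chance imbalance.** The SE of the baseline mean difference is SD × √(2/n). With SD 0.25 and n = 65: 0.25 × √(2/65) = 0.044, so the 95% range is ±0.086. At 65 per arm, SD 0.15 to 0.30 gives a 95% range of ±0.052 to ±0.103. The probability of an absolute baseline difference of 0.03 or more is about 23% (SD 0.15, 72 per arm) to 57% (SD 0.30, 65 per arm).

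**Share carried into the QALY difference.** This is the slope of QALY on baseline utility: b = 0.125 + 0.875r.

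**Precision.** The variance of the QALY is SD² × [(1 − r) × Σw² + r], with Σw² = 2 × 0.125² + 3 × 0.25² = 0.21875. The unadjusted SE is the square root of that variance times √(2/n). R² = b² / [(1 − r) × 0.21875 + r]. The adjusted SE is the unadjusted SE times √(1 − R²).

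| r | b | shift from a one-SE imbalance (0.044) | shift from a 0.05 imbalance | R² | SE unadjusted | SE adjusted | SE cut |
|---|---|---|---|---|---|---|---|
| 0.3 | 0.39 | 0.017 | 0.019 | 0.33 | 0.030 | 0.024 | 18% |
| 0.5 | 0.56 | 0.025 | 0.028 | 0.52 | 0.034 | 0.024 | 31% |
| 0.7 | 0.74 | 0.032 | 0.037 | 0.71 | 0.038 | 0.021 | 46% |

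Under this model b and the percentage cut in SE depend only on r, not on the SD or the numbers per arm. The absolute shifts in the one-SE column scale with the SD. Any gain from the stratification factors, and the small cost of fitting covariates, are left out.

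**The adjustment clause beside the prognostic list.** The clause would have to be read as covering baseline EQ-5D for it to help. The article's own list of prognostic measures does not include EQ-5D. Nothing says what size of difference triggers adjustment, or how an adjusted estimate would enter the bootstrap.

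**The case against.** There are four serious replies.

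1. *The plan never says the QALY difference is unadjusted.* This is right. A reader might infer from the analogy with the RTW ratio that a plain difference of means is the stated plan. The sentence "Bootstrapping will be used for pair-wise comparison of the mean groups" continues with costs only, and the QALY sentence does not rule out an adjusted difference. What the text supports is narrower: it sets a group-difference template and names no covariate.

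2. *The general clause already covers imbalance.* It does reach the economic analyses, because it is not limited to the effect evaluation, and baseline utility could count as prognostic. But it has no variable list and no trigger, and it acts only after the baseline has been inspected. It also treats adjustment purely as a remedy for visible imbalance, so the gain in precision is lost whenever the arms look alike.

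3. *Randomisation makes the unadjusted estimate valid.* It is unbiased on average, and its confidence interval already allows for chance imbalance. A reader might infer that an imbalance passes in full into the result, or that it can reverse the sign by itself. The slopes show partial carry-over. The documents give no expected QALY effect against which a sign change could be judged, and the one-SE shift (0.017 to 0.032) is smaller than the matching unadjusted SE (0.030 to 0.038). What remains is lost precision and bias conditional on the imbalance actually observed.

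4. *An article may leave such detail to the analysis plan.* QALY construction can fairly be left there, and silence on it is not an error. The article does, however, fix a conditional, data-dependent adjustment rule and a template for the ratio, and those can be improved as they stand.

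It is also fair to say that the primary outcome and the cost-per-RTW ratio are not touched.

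**Conclusion.** The point holds as a cheap improvement to the method, not as an error or a contradiction. The article carries a group-difference template over to cost per QALY without naming baseline EQ-5D as a covariate, and leaves adjustment to an undefined rule that depends on the observed data.

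The consequence is an estimate that may be less precise than necessary and, given a chance utility imbalance, biased by about 39% to 74% of that imbalance. Adjustment would cut the SE of the QALY difference by about 18% to 46%. These figures rest on the assumed equal-correlation model with r from 0.3 to 0.7, trapezoid QALYs and EQ-5D at all five times. The absolute values rest further on SD 0.25 and 65 per arm. The documents supply only the numbers per arm and the general schedule. The five-wave EQ-5D schedule is itself an inference: the Outcomes section shows that some instruments (job content and the ASE questions) are used only at baseline and 3 months.

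**What to change.** Add one sentence to the Cost-effectiveness evaluation subsection of Statistical analyses, or to the analysis plan. It should say that the QALY difference is estimated by regression of QALY on arm, baseline EQ-5D utility, company, and full or part-time sick leave. The model is refitted in each bootstrap resample. The adjusted difference is used in the cost-per-QALY ratio, the cost-effectiveness plane and the acceptability curve, whether or not the arms look imbalanced. The unadjusted difference can be shown beside it for transparency.

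State as well that the EQ-5D is completed at baseline and at which follow-up times. If it follows the general outcome schedule, no new data, employees or visits are needed, and the cost is the wording and a few lines of analysis code. The sentence should be fixed before outcome data are compared by arm.
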